# The effectiveness of a stratified group intervention using the STarTBack screening tool in patients with LBP - a non randomised controlled trial

**DOI:** 10.1186/1471-2474-14-342

**Published:** 2013-12-05

**Keywords:** Low back pain, Stratification, STarTBack tool, Group exercise/education Intervention

## Abstract

**Background:**

Low back pain (LBP) is costly to society and improving patient outcomes is a priority. Stratifying LBP patients into more homogenous groups is advocated to improve patient outcome. The STarT Back tool, a prognostic screening tool has demonstrated efficacy and greater cost effectiveness in physiotherapy settings. The management of LBP patients in groups is common but to date the utility of the STarT Back tool in group settings has not been explored. The aim of this study is to determine if the implementation of ‘stratified care’ when delivered in a group setting will lead to significantly better physical and psychological outcomes and greater cost effectiveness in LBP patients compared to a bestcare historical control group.

**Methods/Design:**

This study is a non randomised controlled trial. Low back pain patients recruited from the Waterford Primary Care area (population = 47,000) will be stratified into low, medium or high risk of persisting symptoms using the STarT Back Tool. Low risk patients will be offered a single one off education/exercise class offering positive messages on LBP management in line with recommended guidelines. Medium risk patients will be offered a 12 week group exercise/education intervention addressing their dominant physical obstacles to recovery. A 12 week group cognitive behavioural approach will be delivered to the high risk patients, characterised by the presence of high levels of psychosocial prognostic factors. These patients will be compared with a historical control group where therapists were blinded as to the risk stratification of patients and a generic group intervention was delivered to all patients, irrespective of their initial risk stratification. The primary outcome measure will be disability (Roland Morris Disability Questionnaire). Secondary outcomes will include back pain intensity (Visual Analogue Scale), distress (Distress and Risk Assessment Method), back beliefs (Back Beliefs Questionnaire), health status (Euroqol), global benefit (7 point likert scale), satisfaction (7 point likert scale), cost effectiveness and functional status. Outcome will be measured at baseline, 12 weeks and 6 months.

**Discussion:**

This paper details the rationale, design, methods, planned analysis and operational aspects of a study examining the utility of the STarT Back Tool as a ‘stratification tool for targeted treatment’ in a group intervention.

**Trial registration:**

Current controlled trials: ACTRN12613000431729.

## Background

Low back pain (LBP) is a major public health problem, costly to society and can lead to disabling symptoms for a large percentage of people. Symptoms are persistent, and though many LBP patients cease consulting their General Practitioner (GP) within a relatively short timeframe, 60-80% of people still report pain and disability one year later [1]. With regards to the management of LBP, guidelines recommend that patients are initially offered conservative management in the form of education and exercise/manual therapy/acupuncture or a combination of a physical and psychological treatment if individual interventions prove ineffective [2]. Though the efficacy of these treatment interventions has been established, in general outcomes from studies are at best moderate [3,4], and improving patient outcomes has become a priority amongst researchers.

Traditionally LBP has been broadly categorised into three main groupings: non specific LBP (94%), nerve root pain (5%) and red flag pathology (1%) [5]. The majority of patients with LBP are classified as ‘non specific’ and a generic treatment pathway is administered to all, irrespective of the underlying condition or psychosocial status. It has been argued that this broad classification of LBP is too heterogeneous and that patients with non specific LBP should be sub-divided into more homogenous treatment groups [6,7]. Sub-grouping and delivering targeted treatment interventions has become a key focus for researchers [8-10]. A number of classification systems have been proposed including diagnostic, prognostic and treatment based systems [11,12]. It has been well established that psychosocial factors can lead to the persistence of LBP: low mood, anxiety, catastrophisation and fear avoidance [13,14]. Bearing this in mind, Hill et al. [15] developed a prognostic screening tool the ‘STarT Back’ Tool which stratifies patients on the presence of potentially modifiable physical and psychological prognostic indicators for persisting disabling low back symptoms. Patients are stratified as low, medium or high risk of persisting symptoms and treatment targeted accordingly. The STarT Back Tool was developed in the primary care setting. It is simple to administer, patient friendly, and provides a welcome alternative to the more in-depth psychosocial questionnaires which can be cumbersome in the primary care setting [16]. The efficacy of the STarT Back screening tool has been demonstrated in individual patient management in the physiotherapy setting with both greater clinical and cost effectiveness reported in the targeted subgroups compared to usual care [10]. In view of its proven utility, the STarT Back Tool is gaining more widespread use [17-19] and its inclusion in spinal care pathways has been recommended by the recently formed UK National Spinal Taskforce [20].

Within physiotherapy settings, different models of care exist for the delivery of LBP interventions. The use of group interventions incorporating rehabilitation and promoting self management strategies are well established [2,4]. The reported benefits of group intervention over individual treatment include greater throughput of patients, treatment is more standardised which enhances outcome measurement, a self management approach to treatment is fostered and the delivery of group interventions has proved more cost effective [21]. From a patient’s perspective, it proves enjoyable and allows patients to meet others with a similar disposition [22,23]. To date, the STarT Back tool has demonstrated efficacy when physiotherapy treatment has been administered on an individual basis. This study aims to explore the utility of the STarT Back Tool in a group setting.

## Methods/Design

### Aims

The main objective of this study is to determine if the implementation of ‘stratified care’ when delivered in a group setting will lead to significantly better physical and psychological outcomes in a group of patients with non specific LBP, compared to a matched best care historical control. The historical control group will consist of individuals who attended the Back Pain Clinic between 2008 and 2011. Evaluation of treatment effect will be made within each of the stratified treatment groups and comparisons will be made between the stratified group outcomes and best care historical control. Secondary analysis will compare the delivery costs of the historical and stratified interventions.

### Hypotheses

The following hypotheses will be tested.

1 Patient stratified to the ‘high risk’ intervention based on the STarT Back tool will have better physical and psychological outcomes compared with their baseline scores and compared with the high risk historical control group.

2 Patients stratified to the ‘medium’ and ‘low risk’ groups based on the STarT Back tool will have significantly better physical and psychological outcomes compared with their baseline scores and equally good outcomes compared with the best-care historical control.

### Study design

This study is a non randomised controlled trial comparing a new stratified intervention to a historical control treatment, which is usual non-stratified care. The trial is thus pragmatic in nature and aims to establish the effectiveness of a treatment intervention in routine everyday practice [24]. The study will determine if the implementation of stratified care in a group setting, using the STarT Back risk stratification tool will result in significantly better physical and psychological outcomes in LBP patients, compared with historical control data collected between 2009–2011 [25]. Patient assessments will occur at baseline, at 12 weeks and 6 months following commencement of the treatment intervention. The primary endpoint for analysis is 6 months. Recruitment will take place between February 2012 and June 2013.

This type of study design may be at risk of selection bias, but the choice of historical controls was made to allow comparability of interventions within a single clinical centre, thus removing the risk of differences in management between centres. Furthermore, since the new treatment paradigm necessitated a shift in management approach to include cognitive behavioural principles with subsequent staff training, the selection of historical controls averted any possible loss of fidelity of the routine care treatment which might have occurred if controls were recruited concurrently to the new intervention group. Other measures taken to minimise potential differences between the intervention and control treatments include; the control and historical interventions will be delivered to the same local population, referred from the same sources, using standard diagnostic and referral criteria. Both the historical and new interventions will be applied in the same clinical setting by therapists who will apply the pre and post treatment assessments in a standardised manner. The same end points will be chosen for the stratified treatment group as has been the practice for the historical controls and there will be no time lag between the historical data collection and the stratified intervention phase. This can be considered an appropriate design in the current study setting, where we have a large dataset documenting existing routine evaluation of clinical treatment outcomes [25]. Here the comparison of interest is between the existing standard management of LBP (the historical control group), in a single centre, to a new paradigm of care (intervention).

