**Figure 1 F1:**
[figure not shown]
Study flow chart.

The historical control consists of patients who attended the Back Pain Clinic between 2009–2011. These patients were referred from the 10 GP practices and their associated physiotherapy services within the Waterford City Primary Care area in exactly the same manner as the intervention group. The patients completed a copy of the same self report questionnaires as the intervention group. In the control group, risk stratification was performed by an independent party (administrator at the clinic) after the initial assessment using the STarT Back scoring algorithm. The therapists were blinded as to the risk stratification of each patient until completion of the treatment intervention at three months. Patients in the historical control group were assessed as routine care which included history taking, a physical examination, review of completed self report questionnaires and performance of timed functional outcome measures in exactly the same manner as the intervention group. Following initial assessment if patients were deemed suitable, all patients irrespective of their risk stratification were entered into a generic 12 week group exercise/education intervention. Consent was obtained retrospectively for the inclusion of these historical controls in line with the National Consent Policy [27].

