#### Best care historical control

The historical control consists of patients who attended the clinic between 2009–2011 [25]. Patients were stratified using the STarT Back screening tool but a non-targeted (‘one treatment fits all’) model of care was delivered to patients. All patients undertook the same generic 12 week group education/exercise programme promoting self management and rehabilitation. The efficacy of this intervention has been established [25] and subsequently this template was utilised to develop the medium and high risk interventions. Similar to the medium and high risk interventions, the historical control comprised two phases. In phase one, patients attended once weekly for four weeks and each class was 1.5 hours in duration. Sessions included exercise and back educational information similar to the ‘medium risk’ intervention already described. In phase two, patients continued independently with the structured home exercise programme for a further eight weeks. Each group consisted of six to ten patients. Validated self report and objective physical outcome measures monitored progress at baseline and at 12 weeks. Outcomes utilised included disability (Roland Morris Disability questionnaire (RMDQ)) [31], pain (Visual Analogue Scale (VAS)) [32], distress (Distress and Risk Assessment Method (DRAM)) [33], back beliefs (Back Beliefs Questionnaire (BBQ)) [34], Simmond’s Functional Tests [35] and lumbar flexibility [36].

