			**(months)**
	Demographics	Age, gender, duration of LBP, employment status, educational attainment, medico-legal status	0
Primary	Back pain disability	Roland and Morris Disability Questionnaire	0,3,6
Secondary	Pain	Visual analogue scale	0,3,6
	Distress	Distress and Risk Assessment Method	0,3,6
	Beliefs	Back Beliefs Questionnaire	0,3,6
	Preference based health utility	EQ-5D	0,3,6
	Global perceived benefit	Compared to symptoms at baseline (7 point likert scale)	0,3,6
	Satisfaction scale	Satisfaction with care received (7 point likert scale)	0,3,6
	Objective spinal mobility	Range of motion T-12 & S1	0,3
	Objective physical function	Simmond’s Tests:	0,3
		sit-stand, forward reach, 50-foot walk test	

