### Analyses

All data will be entered into the IBM Statistical Package for the Social Sciences [39] and subsequently cleaned and checked for normality. Baseline differences between the treatment groups will be explored with independent t tests and chi square tests. Preliminary analysis will compare pre to post intervention outcomes for each treatment group to determine if a significant treatment effect is achieved by each of the stratified interventions using paired t-tests and Cohen’s d effect size statistics. The main analysis will compare treatment response between the stratified and control groups using analysis of covariance (ANCOVA) models with baseline measures as the covariate and treatment group as the between group factor. Statistical significance will be set at p < 0.05. Missing data will be imputed using the linear and logistic regression models applied by the multiple imputation functions in SPSS and an intention to treat analysis will be performed. We will also conduct a complete case analysis for those cases where we have complete follow up data. In the event of non normal data, non parametric tests will be performed instead. Exploratory economic analyses will be undertaken. Costs of each intervention will be calculated and quality-adjusted life years (QALYs) gained computed. These will be compared between interventions using independent t tests. Six month health care utilisation attendances and associated costs will be calculated for each patient and compared between the intervention groups using chi square tests for categorical data and t tests for continuous data.

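### The primary time point is 6 months, but the only assessment schedule given for the historical controls is baseline and 12 weeks, so the primary between-group comparison has no documented control outcome

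*Protocol article*

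**What the plan says.** All references are to the protocol article.

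- **Primary time point.** Study design: "The primary endpoint for analysis is 6 months". The same section gives the schedule, in the future tense: "Patient assessments will occur at baseline, at 12 weeks and 6 months following commencement of the treatment intervention". Table 2 lists the primary outcome as "Roland and Morris Disability Questionnaire 0,3,6" (months).
- **Main comparison.** Aims, Hypotheses and Analyses all set the stratified groups against the historical controls. The main analysis is an ANCOVA with the baseline value as covariate. Analyses does not name the time point for that model.
- **Control schedule.** Best care historical control: "Validated self report and objective physical outcome measures monitored progress at baseline and at 12 weeks". The list of measures that follows includes the RMDQ.
- **Stated parity.** Study design: "The same end points will be chosen for the stratified treatment group as has been the practice for the historical controls".
- **Missing data.** Analyses: "Missing data will be imputed using the linear and logistic regression models applied by the multiple imputation functions in SPSS", together with an intention-to-treat analysis and a complete case analysis.

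**The concern.** A controlled comparison needs the outcome in both groups at the same time point. The article names 6 months as primary, but the control group is a past cohort whose documented follow-up stops at 12 weeks. New data cannot be collected at the right time for patients treated in 2009–2011, and an analysis plan can specify a model but cannot supply outcomes that were never recorded.

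The between-group part of each hypothesis is at stake: superiority in the high-risk stratum, and non-inferiority in the medium- and low-risk strata. If 6-month control scores do not exist, an analyst following the text has three routes, none of which gives a valid 6-month contrast:

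- run the model with no controls;
- fill in every control value by imputation;
- set 6-month treated scores against 12-week control scores, which mixes treatment with length of follow-up.

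The article prescribes none of the three for the controls, but it excludes none of them either.

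**Working it through.** **1. The plan's own sample size (Sample size and statistical power).** Inputs: effect size 0.38, two-sided alpha 0.05, power 80%, pre–post correlation 0.592.

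- Unadjusted, normal approximation: n = 2 × (1.960 + 0.842)² / 0.38² = 108.7 per group. The t-based value is 109.68.
- ANCOVA factor: 1 − 0.592² = 0.6495.
- Adjusted: 108.7 × 0.6495 = 70.6, so 71 (normal); 109.68 × 0.6495 = 71.24, so 72 (t-based).

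The stated 72 per high-risk group is reproduced. The total is also consistent: 2 × 72 + 4 × 57 = 372. I take the 57 per group as stated, since this point does not depend on it. The calculation presumes an observed outcome in both groups at the analysis time.

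**2. Documented outcomes by group and time point.**

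| Time | Stratified groups | Historical controls |
|---|---|---|
| Baseline | yes (Study design, Table 2) | yes (Best care historical control) |
| 12 weeks | yes (Study design, Table 2) | yes (Best care historical control) |
| 6 months | yes, postal (Follow up assessment) | not described anywhere |

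Planned minimum number of controls: 72 + 57 + 57 = 186, which is 186/372 = 50% of the total. As described, up to 186 controls can contribute at 12 weeks and none at 6 months.

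**3. Supporting text.** The 6-month follow-up is written prospectively: an advance text message, a postal questionnaire and a telephone call. Nothing similar is described for the controls. Their programme was four weeks of classes plus eight weeks at home, ending at week 12. The text below Figure 1 puts its end at the same point: "The therapists were blinded as to the risk stratification of each patient until completion of the treatment intervention at three months".

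**4. What imputation would do if all 6-month control values were absent.** Let Y0, Y3 and Y6 be RMDQ at baseline, 12 weeks and 6 months, and let G = 1 for stratified care and 0 for control.

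- Only stratified patients have Y6, so the imputation model is estimated in them alone: E[Y6] = a + b·Y0 + c·Y3. A coefficient for G cannot be estimated.
- Write the 12-week ANCOVA as E[Y3] = m + k·Y0 + d3·G, where d3 is the 12-week treatment contrast.
- Using the same a, b and c for the controls gives E[Y6] = (a + c·m) + (b + c·k)·Y0 + (c·d3)·G.

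The 6-month contrast is therefore c × d3: the 12-week contrast multiplied by a slope learned from stratified patients only. If Y3 were left out of the imputation model, the contrast would be zero by construction. Either way the result comes from the model and not from control outcomes at 6 months. If c lies between 0 and 1, the contrast shrinks toward zero, which would favour a non-inferiority conclusion. A complete case analysis at 6 months would contain no controls.

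**The case against.** The strongest reply is that the article never says the controls were measured at those two times and no others. The sentence on control assessments may be incomplete: the controls are said to have completed the same self-report questionnaires as the intervention group, yet the list under Best care historical control omits the EQ-5D. Study design refers to a large existing dataset and to shared end points, and Table 2 does not restrict its 0, 3 and 6 month schedule to one group. Figure 1 and the cited report of the historical cohort might settle the matter, and neither can be seen here.

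This stands as a limit on certainty. It does not remove the conflict, because no section documents a 6-month control assessment and the schedule that includes 6 months is prospective.

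A reader might go further in four ways that the document does not support:

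- **That 6-month control data are known not to exist.** This is inferred from one sentence and from silence elsewhere.
- **That the parity statement is false.** It conflicts with a 6-month endpoint only if end points there includes timing. If it means instruments, it can be true, and the 6-month gap remains.
- **That the plan intends to impute every control value.** Analyses describes ordinary multiple imputation and does not mention this case. Wholesale imputation is something the text permits, not a step it states.
- **That both hypotheses fail entirely.** Each also has a within-group part, which can be tested at 6 months in the stratified groups, and the between-group part can be estimated at 12 weeks.

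**Conclusion.** The point holds in conditional form. The article fixes a primary time point for which it documents no outcome in the control group, and the sections on study design, control care and analysis must be reconciled.

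If 6-month control RMDQ scores were not collected, the primary between-group contrast is not estimable from observed data in any of the three risk strata. None of the planned minimum of 186 controls would contribute, and multiple imputation could not identify the contrast. The figure of 186 is a planned minimum, not a count of patients known to lack data. If the scores were collected, the error is confined to an incomplete description of the controls.

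Confidence is high that the text is inconsistent, and lower that the data are absent. In either case the correction is needed before the outcome analysis.

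**What to change.** 1. Establish whether RMDQ scores at 6 months exist for the historical controls.
2. If they do, correct the section on the historical control to say so. State how many there are in each risk stratum and how they were collected. The 6-month primary endpoint can then stay.
3. If they do not:
   - make 12-week RMDQ, the one post-baseline time point documented for both groups, primary for every stratified-versus-control comparison, superiority and non-inferiority alike;
   - name that time point in the ANCOVA description;
   - report 6-month RMDQ only as maintenance of change within the stratified cohort;
   - state that 6-month control values will not be imputed, and that 6-month treated scores will not be compared with 12-week control scores.
4. In either case, reword the parity statement so that it says whether it covers instruments, timing or both.

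**Cost.** No new data are needed. The sample size formula does not depend on the time point, but the authors should confirm that the SD of change (4.7) and the correlation (0.592) apply at 12 weeks, because the article does not say when the later measurement was taken. If the primary time point moves, the controlled claim is limited to 12 weeks. It would also be a late change to a published plan: the article appeared in December 2013, the month follow-up was due to finish, with results planned for April 2014. It therefore needs a dated, justified amendment made before outcome analysis.
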